### Planned analyses

Although considerable previous observational work suggest that both procedures are safe [21,26,28,30,32,83-86], safety will be evaluated by an external committee (DSMB) in conjunction with the steering committee (who will retain executive power). DSMB meetings will be held after the 1^st ^and 2^nd ^years of enrollment. The DSMB report will be evaluated by the steering committee and JOINTS Canada. No interim analyses are planned as both short and long-term outcomes are of interest, the probability of safety issues is very low, and because clinically important milestones exist across the spectrum of evaluations. As the primary outcome is quality of life, it is important to have a fully powered 2-year outcome.

We will conduct the analysis by pooling the data across designs (expertise-based and conventional), comparing the outcomes of patients who underwent mini-open versus all-arthroscopic. Pooling this data assumes that the design has no affect on the treatment effect. To test this assumption, we will test for heterogeneity of the results between studies using a formal assessment of the variability of results across studies by conducting statistical tests that provide an I^2 ^value. The I^2 ^value estimates the percentage of total variation in results across studies that are due to heterogeneity between studies rather than that due to chance. Low, moderate, and high levels of heterogeneity are roughly categorized by I^2 ^values of 25%, 50%, and 75% respectively. If the I^2 ^value is greater than 25%, we will perform a formal test of the interaction term to determine whether there was a significant difference in the treatment effect between groups, depending on which study design was used [87]. As indicated above, we will also monitor aspects of trial conduct including the potential numbers of patients at test sites, the recruitment rates, and the rate of study protocol violations.

In our primary analysis we will use an analysis of covariance (ANCOVA), where the baseline WORC score is used as a covariate, to compare the quality of life (WORC score) at 2 years post-operatively[88-91]. As a secondary analysis, we will conduct the same statistical test but will include age and tear size as covariates with the baseline score. All outcome measures with a continuous metric will be analyzed in the same manner (ASES, range of motion, MRI (degree of muscle atrophy, degree of fatty infiltration, remaining tear size), Work Limitations, strength, and SF-12). We will also conduct a repeated-measures ANCOVA to determine whether quality of life (as the primary outcome) changed differently over time between groups.

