### Sample size

We have previously completed a non-randomized pilot study (n = 36, [name]) comparing mini-open to all-arthroscopic rotator cuff repair and have data representative of the population we wish to sample for this study. We piloted a number of study outcomes, but our calculations are based on our planned primary outcome measure (WORC). From our pilot data, the baseline WORC scores were 1345/2100 (SD = 324) for mini-open patients and 1463(287) for arthroscopic repair. At 1 year, patients in the mini-open group had a mean score of 712.5 (SD = 650.7) and the patients in the all-arthroscopic group had a mean score of 940.6 (a difference of 228 points on the WORC). In our estimates of sample size requirements, we have used an estimated standard deviation of 450 since we suspect that the standard deviation observed in the pilot study at 1 year is larger than that expected at 2 years since patients are expected to be more stable in their outcomes by this time point. Further evidence to support our hypothesis comes directly from our pilot data where the estimate of standard deviations from the baseline assessment was 287 and 325. We will perform an analysis of covariance (ANCOVA) using the baseline WORC scores as a covariate to determine whether there is a statistically significant and clinically important difference between treatment groups at 2 years post-operative. We defined a clinically important difference as a 20% difference in the mean score between groups [47]. We used the following equation to calculate the sample size:

Calculation: N per group = 2((Z_α _+ Z_β_)^2^σ^2^(1-r^2^))/(δ)^2^, Where:

α = the probability of making a Type I error = 0.05

1-β = the power to detect a difference if one truly exists = 0.80, thus, β = 0.20

δ = 20% of the baseline mean score = 142.5*

r = correlation between baseline and post-operative data = 0.55

σ = standard deviation = 450

N per group = 2((1.96 + 0.84)^2 ^(450)^2^(1-0.55^2^))/(142.5)^2 ^= 109 patients per group

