### Arrangements for allocating participants to trial groups

Seven centres across Canada are participating in this trial (London, Calgary, Toronto, Vancouver, Edmonton, New Westminster, Winnipeg). All surgeons (n = 15) have been assigned to a design that will minimize the impact of expertise on study outcomes. Those with > 2 years recent experience in both procedures will require conventional design. Surgeons with primary expertise in only one procedure are paired with those with expertise in the alternative procedure from the same site and subject to expertise-based design. In both designs, the randomization scheme will be stratified by surgeon and compensation status (Workplace Safety and Insurance Board (WSIB), litigation or disability). We will use variable permuted block sizes to randomize patients on a 1:1 ratio; block sizes will remain confidential to the biostatistician to protect the integrity of the randomization scheme. Local research assistants will identify all patients (eligible participants, eligible non-participants and non-eligible), reasons for ineligibility or refusal, and obtain consent from eligible patients.

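### The primary ANCOVA leaves out the randomisation strata (surgeon or surgeon pair, and compensation status), so its standard error is miscalibrated if those factors are prognostic, in opposite directions in the two designs

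*Protocol article*

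**What the plan says.** Under Arrangements for allocating participants to trial groups, the Protocol article says that in both designs "the randomization scheme will be stratified by surgeon and compensation status (Workplace Safety and Insurance Board (WSIB), litigation or disability", with 1:1 allocation in variable permuted blocks. Fifteen surgeons at seven centres are each assigned to one design. In the conventional design a surgeon performs both procedures. In the expertise-based design a surgeon skilled in one procedure is paired with a colleague at the same site skilled in the other, and the patient is randomised between the two. The stratum there is most naturally read as the pair, since the operating surgeon is the thing being allocated. Two centres run both designs, and the Expertise-based RCT section says design is block randomised there too.

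The Planned analyses section fixes the model: "In our primary analysis we will use an analysis of covariance (ANCOVA), where the baseline WORC score is used as a covariate". The secondary model "will include age and tear size as covariates with the baseline score". The abstract repeats both. Data are pooled over designs. Design is examined through I² and, above 25%, a test of interaction with treatment. It is not a term in the primary model, and no section adjusts for surgeon or compensation status or allows for clustering by surgeon.

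**The concern.** Stratified blocks hold the arms nearly equal on the stratifying factors, so the treatment difference no longer varies with those factors from one randomisation to another. An analysis that ignores them still counts their variance as residual noise. The model-based standard error then exceeds the true one, the test is conservative, and precision that the stratification has secured is not used.

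That reasoning needs the factor to be balanced across arms. It applies to compensation status and to surgeons in the conventional design. It does not apply to the operating surgeon in the expertise-based design. There the pair is balanced, but each operating surgeon treats one arm only. Differences between surgeons add to the variance of the treatment difference, and a model that treats patients as independent misses this. The standard error is then too small and the test too liberal.

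At stake are the calibration of the primary p value and confidence interval, and a modest amount of power.

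**Working it through.** **The plan's own figure.** Inputs, all from the Sample size section: "α = the probability of making a Type I error = 0.05"; "1-β = the power to detect a difference if one truly exists = 0.80"; "δ = 20% of the baseline mean score = 142.5"; "σ = standard deviation = 450"; "r = correlation between baseline and post-operative data = 0.55".

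- Residual variance after baseline WORC: 450² × (1 − 0.55²) = 141,244, so the residual SD is 375.8.
- N per group = 2 × 2.8² × 141,244 / 142.5² = 109.07. The stated 109 reproduces.
- Total: 109 × 1.15 × 2 = 250.7. The stated 250 reproduces.
- Only baseline WORC is credited with reducing variance.

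**Balanced strata (compensation status, conventional-design surgeon).** Let R² be the share of residual variance that the strata explain. The article gives no value; I assume 0.05 to 0.15. With 15% lost, 250 × 0.85 / 2 = 106 per arm remain, and the unadjusted model SE is 375.8 × √(2/106) = 51.6, so δ/SE = 2.760.

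- Model SE over true SE = 1/√(1 − R²)
- True type I error = 2 × [1 − Φ(1.96/√(1 − R²))]
- Power, strata omitted = Φ((2.760 − 1.96)/√(1 − R²))
- Power, strata included = Φ(2.760/√(1 − R²) − 1.96)

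| R² | SE ratio | Type I error | Power, omitted | Power, included | Points forgone |
|---|---|---|---|---|---|
| 0 | 1.000 | 5.0% | 78.8% | 78.8% | 0 |
| 0.05 | 1.026 | 4.4% | 79.4% | 80.8% | 1.4 |
| 0.15 | 1.085 | 3.4% | 80.7% | 84.9% | 4.2 |

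The omitted-strata power must use the reduced true SE, since the estimate itself has gained from the balance. It therefore rises slightly with R² and does not fall below the R² = 0 value.

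These figures assume perfect balance, which small strata and incomplete blocks will not deliver. A simulation with 218 analysed patients, all 15 surgeons conventional, a surgeon share of 5% and a compensation share of 10% gave a baseline-only type I error of 0.038, a model SE of 50.9 against a true SE of about 48, and power of 81% rising to 85% with adjustment. The SE was thus about 6% too large, where the formula gives 8.5%.

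**Operating surgeon nested in arm (expertise-based design).** The article does not say how many surgeons are in pairs. Assume 7 conventional surgeons and 4 pairs, a surgeon share of 5%, no compensation effect, 109 patients per arm and equal load per surgeon (218/15 = 14.5 patients).

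- Patient-level part of the variance: 0.95 × 141,244 × 2/109 = 2,462.
- Part from the 8 paired surgeons: 8 × (14.53/109)² × 0.05 × 141,244 = 1,004.
- True SE = √3,466 = 58.9. Model SE = 375.8 × √(2/109) = 50.9.
- Type I error = 2 × [1 − Φ(1.96 × 50.9/58.9)] = 0.090. Simulation of this layout gave 0.088.

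With 7 pairs and one conventional surgeon, simulation gave about 0.13.

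**Would fixed stratum effects alone repair this?** With 4 pairs, a surgeon share of 5% and a compensation share of 10%, two simulations gave baseline-only type I errors of 0.060 and 0.084. With fixed effects for surgeon or pair and compensation status they gave 0.080 and 0.105. In both, fixed strata shrink the model SE while the true SE hardly moves. The level is sensitive to how many patients each paired surgeon treats: if load is equal per stratum (218/11 = 19.8 patients, 9.9 per paired surgeon), the surgeon part above drops from 1,004 to 8 × (9.91/109)² × 0.05 × 141,244 = 467.

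**The case against.** The case for leaving the model alone has substance. The article gives no surgeon or compensation variance, so every size above rests on an assumption. If the strata add little beyond baseline WORC, nothing is lost. The article gives no reason for stratifying by compensation status, so it cannot be cited as declaring that factor prognostic. For surgeons it goes further: the section on expertise-based allocation treats better outcomes with more experienced surgeons as established. The sample size credits baseline WORC only and so agrees with the stated model. Design is also not ignored, since its effect on the treatment difference is to be examined. All of this stands and limits the size of the point, but it does not remove the mismatch between allocation and analysis. Nor is this a detail left to an unseen analysis plan, because the article names both covariate sets.

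A reader might infer more than the document supports:

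- **That the trial is underpowered because of the omission.** It is not. Where strata are balanced, omitted-strata power is at or slightly above its R² = 0 value.
- **That the standard error is too large throughout.** This fails for operating surgeons in the pairs, where the error runs the other way.
- **That pooling without a design term lets unequal arm ratios by design bias the estimate.** Allocation is 1:1 in permuted blocks in both designs, so imbalance is limited to incomplete blocks and the effect is negligible.
- **That adding the strata as fixed effects is enough.** The simulations show that it does not repair the nested part and can worsen it.

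**Conclusion.** The point holds in a limited form. The stated primary model does not reflect the stated randomisation. For compensation status and conventional-design surgeon, assumed to explain 5% to 15% of residual variance and to be balanced across arms, the unadjusted SE is up to 2.6% to 8.5% too large, type I error is about 4.4% to 3.4%, and 1.4 to 4.2 points of power are forgone at 106 per arm. For the expertise-based part the SE is too small if surgeons differ. Under an assumed 5% surgeon share, simulated type I error for the whole trial ran from about 0.06 to 0.09 with four pairs, depending on the compensation share and probably on patients per surgeon, and reached about 0.13 with seven pairs. The net direction for the pooled analysis depends on the number of pairs, their caseload and the surgeon variance, none of which the article gives. If neither surgeon nor compensation status is prognostic, there is no effect. This should be changed, but it does not threaten the stated 80% power.

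**What to change.** In Planned analyses and in the abstract, define the primary model as 2-year WORC on:

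- treatment and baseline WORC;
- compensation status;
- randomisation stratum: surgeon in the conventional design, surgeon pair in the expertise-based design;
- a random operating-surgeon effect for the expertise-based part, with small-sample degrees of freedom.

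Do not add a separate fixed design term. Every surgeon belongs to one design, so design is fully determined by surgeon or pair and would be aliased. Do not enter operating surgeon as a fixed effect in the pairs either, because within a pair it coincides with treatment. The planned check of treatment-by-design heterogeneity can stay, and the age and tear-size model remains secondary.

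The change needs no new data, as the factors are known at randomisation. Its costs are a slightly more complex model, few pairs from which to estimate the surgeon variance, and possibly a wider confidence interval from the expertise-based part. That widening would reflect real uncertainty that the present model leaves out.

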### Expertise-based random allocation may enhance feasibility and validity

In 1980, randomizing subjects to clinicians was first suggested by Van der Linden [36,37]. Since that time, however, this design has been little used. The expertise-based randomized controlled trial has been recently revisited as a potential alternative to minimizing these barriers [34]. In a conventional RCT, both interventions are offered by each health care provider. This works well in drug trials where there is no interaction between the drug and its provider and where the provider can be blinded to the intervention they are dispensing. However, in surgical trials there are problems with this approach that have been recently described by the Expertise-Based Group [34]. The primary concern is that the conventional RCT may actually introduce a bias, due to "differential expertise" within a treatment group that may act as a confounder leading to spurious or biased results. It has been well established that the patients of surgeons who have more experience can expect better outcomes following a surgical intervention. Thus, the patients of surgeons participating in a conventional clinical trial will tend to have better outcomes if they are assigned to the treatment in which their surgeon is more experienced. Greater imbalance in expertise between surgeons compounded by an imbalance in recruitment rates between surgeons will result in greater differential expertise bias and lower trial validity. In fact, extensive experience may be required to achieve superior outcomes. Thus, conducting a specific number of "run-in cases" prior to enrolling patients (used in conventional RCTs) does little to impact on this form of bias.

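### Surgeon is nested in arm in the expertise-based part, but the primary ANCOVA and the sample-size formula treat patients as independent; if surgeons differ, the standard error is too small and 80% power is optimistic

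*Protocol article*

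**What the plan says.** **Model.** Planned analyses pools the two designs and names the primary model: "In our primary analysis we will use an analysis of covariance (ANCOVA), where the baseline WORC score is used as a covariate". The secondary version adds only age and tear size. No surgeon term, random effect or cluster-robust error is mentioned.

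**Design.** The section on allocating participants lists 15 surgeons at seven centres. Those experienced in both procedures work in the conventional design and operate in both arms. For the others: "Surgeons with primary expertise in only one procedure are paired with those with expertise in the alternative procedure from the same site". Under Expertise-based RCT, the patient is randomised to a surgeon, and the surgeon determines the procedure. Randomisation is stratified by surgeon and compensation status.

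**Rationale.** The background section on expertise-based allocation states: "It has been well established that the patients of surgeons who have more experience can expect better outcomes following a surgical intervention".

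**Sample size.** The inputs are "α = the probability of making a Type I error = 0.05", "1-β = the power to detect a difference if one truly exists = 0.80", "δ = 20% of the baseline mean score = 142.5", "σ = standard deviation = 450" and "r = correlation between baseline and post-operative data = 0.55". They give 109 per group, raised by 15% to 250 in total. The formula has no term for clustering by surgeon.

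**The concern.** Where a surgeon operates in both arms, that surgeon's effect largely cancels from the treatment difference. Where a surgeon operates in one arm only, it does not: the difference between the two members of a pair is part of the estimated treatment effect, and adding patients to the pair does not average it away. A model that treats patients as independent counts this as patient-level noise and divides it by the number of patients, although it comes from only a few surgeons.

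At stake are the width of the primary confidence interval and the size of the primary test. A chance difference between a few surgeons could be read as a difference between operations. The planned power rests on the same omission.

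**Working it through.** **1. The plan's own figure.** N per group = 2 × (1.96 + 0.84)² × 450² × (1 − 0.55²) / 142.5² = 2 × 7.84 × 202,500 × 0.6975 / 20,306.25 = 109.07. Then 109 × 1.15 × 2 = 250.7. Both 109 and 250 reproduce, and power at 109 per group is 79.9%. All of this assumes independent patients.

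**2. Patients per surgeon, m.** 250 less 15% is 212.5, and 212.5 / 15 = 14.2. From 109 per group, 218 / 15 = 14.5. I use m = 14 for the variance ratios and 14.5 for power, with equal caseloads.

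**3. Share of patients in the expertise-based part, f.** The number of pairs is not stated. The Expertise-based RCT section puts pairs at two centres, so at least 4 surgeons are nested. The same two centres also have conventional surgeons. With strict pairing of an odd total of 15, at least 3 must be conventional, which leaves at most 12 nested. So 2, 4 and 6 pairs (f = 4/15, 8/15, 12/15) span the range.

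**4. Variance ratio.** Let ρ be the share of baseline-adjusted variance due to the operating surgeon. The nested part has variance factor 1 + (m − 1)ρ. The crossed part has 1 − ρ, because the surgeon effect cancels. Weighting by f and 1 − f:

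true / model variance = f[1 + (m − 1)ρ] + (1 − f)(1 − ρ) = 1 + ρ(f·m − 1)

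The ratio exceeds 1 for any positive ρ once f·m > 1. With 2 pairs, f·m = (4/15) × 14 = 3.7.

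**5. Type I error** = 2[1 − Φ(1.96 / √ratio)]. The protocol gives no ρ, so the values below are assumed.

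| Pairs | Variance ratio at ρ = 0.02 / 0.05 / 0.10 | Type I error |
|---|---|---|
| 2 | 1.05 / 1.14 / 1.27 | 6% / 7% / 8% |
| 4 | 1.13 / 1.32 / 1.65 | 7% / 9% / 13% |
| 6 | 1.20 / 1.51 / 2.02 | 7% / 11% / 17% |

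Worked example, 4 pairs at ρ = 0.05: 1 + 0.05 × (7.47 − 1) = 1.32; 1.96 / √1.32 = 1.70; two-sided tail 9%.

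**6. Simulation check.** The baseline-only ANCOVA was simulated with no treatment effect (20,000 trials per cell, 218 patients, 15 surgeons). It rejected in 5.5% / 6.8% / 8.8% of trials with 2 pairs, 6.5% / 9.2% / 13.7% with 4, and 7.7% / 11.6% / 17.7% with 6. With ρ = 0 it rejected in about 5%. With no pairs and ρ = 0.05 it rejected in 4.6%, so the crossed part is slightly conservative; the figures above already include that offset. Adding a centre ICC of 0.05 at ρ = 0.05 still gave 6.5%, 8.7% and 11.1%.

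**7. Power at 109 per group with surgeon variance counted** = Φ(142.5 / SE − 1.96), where SE = 450 × √0.6975 × √(2/109) × √ratio = 50.9 × √ratio.

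| Pairs | ρ = 0.01 | 0.02 | 0.05 | 0.10 |
|---|---|---|---|---|
| 2 | 79% | 78% | 75% | 69% |
| 4 | 77% | 75% | 68% | 58% |
| 6 | 76% | 72% | 62% | 50% |

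These are normal approximations; small-sample degrees of freedom lower them further.

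**The case against.** **The surgeon effect may be small.** The ICC is assumed. The rationale speaks of experience, and the design works to even that out: conventional surgeons need more than two years' recent experience in both procedures, paired surgeons stay within their expertise, and surgery and rehabilitation follow a protocol. Pairs share a site, so centre differences cancel, and random assignment to surgeon removes case-mix differences on average. This stands as a reason to take the low end seriously. At ρ = 0.01 the type I error is only 5.3% to 6.2%. It does not justify setting the effect to zero, because surgeons of equal experience can still differ.

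**The target of inference.** If the question is only how these 15 surgeons do with their assigned procedures, individual randomisation keeps the test at 5%. That is correct. But the primary objective is worded as a comparison of the procedures, and the abstract's discussion claims definitive international evidence.

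**Existing safeguards.** Stratification by surgeon cannot balance surgeons across arms when each works in one arm. The I² and interaction check compares the two designs; it might hint at a problem but does not correct the standard error.

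**An article condenses.** Details of clustering may be left to an analysis plan. Here, however, the article itself states the primary model with its covariate and the sample-size formula.

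**Stronger readings.** A reader might apply the fully nested design effect, 1 + (m − 1)ρ, to the whole trial. The allocation sections rule that out, because conventional surgeons operate in both arms. A reader might also infer that the error rate certainly and materially exceeds 5%. The documents do not support that without a positive surgeon effect, inference beyond these surgeons, and a known number of pairs.

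**Conclusion.** The point holds conditionally. The direction is firm across every number of pairs that the protocol allows, given any positive surgeon effect and inference about the procedures. The size is open: from barely above 5% (2 pairs, ICC 0.01) to about 17% (6 pairs, ICC 0.10). The mild end is as compatible with the documents as the severe end. The figures rest on equal caseloads, strict pairing, about 14 evaluable patients per surgeon and assumed ICCs. The point concerns precision and power; it does not show that the treatment estimate is biased in favour of either procedure.

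**What to change.** Specify the primary model as a linear mixed model: treatment and baseline WORC as fixed effects, a random intercept for operating surgeon, and small-sample degrees of freedom (for example Kenward-Roger). Keep the plain ANCOVA as a sensitivity analysis. Fixed surgeon effects would not serve, because within each pair they are confounded with arm.

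In a simulation with 15 surgeons and 14 patients each, across 2 to 6 pairs and ICC 0.02 to 0.10, the random intercept brought type I error to about 5–7% with normal critical values and 3–5% with a t on 13 degrees of freedom. The small-sample correction therefore matters and may be slightly conservative.

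In the sample-size section, state the number of pairs, say that 80% power assumes no surgeon effect, and give power across ICC 0.01 to 0.10.

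**Cost.** Wording only as regards data, since surgeon is a stratification factor and is already recorded. The interval will be wider and the stated power visibly lower. More patients from the same surgeons are an inefficient remedy. With 15 surgeons, the evaluable number per group for 80% power is (1 − ρ) / (1/109.2 − ρ·f·2/15), where 109.2 is the figure without a surgeon effect. At ICC 0.05 this gives about 129, 170 and 249 for 2, 4 and 6 pairs. With 6 pairs at ICC 0.10, no number of patients is enough.

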**Methods/Design:**

This randomized, multi-centre, national trial will determine whether an arthroscopic or mini-open repair provides better quality of life for patients with small or moderate-sized rotator cuff tears. A national consensus meeting of investigators in the Joint Orthopaedic Initiative for National Trials of the Shoulder (JOINTS Canada) identified this question as the top priority for shoulder surgeons across Canada. The primary outcome measure is a valid quality-of-life scale (Western Ontario Rotator Cuff (WORC)) that addresses 5 domains of health affected by rotator cuff disease. Secondary outcomes will assess rotator cuff functionality (ROM, strength, Constant score), secondary dimensions of health (general health status (SF-12) and work limitations), and repair integrity (MRI). Outcomes are measured at baseline, at 6 weeks, 3, 6, 12, and 24 months post-operatively by blinded research assistants and musculoskeletal radiologists. Patients (n = 250) with small or medium-sized cuff tears identified by clinical examination and MRI who meet eligibility criteria will be recruited. This sample size will provide 80% power to statistically detect  a clinically important difference of 20% in WORC scores between procedures after controlling for baseline WORC score (α = 0.05). A central methods centre will manage randomization, data management, and monitoring under supervision of experienced epidemiologists. Surgeons will participate in either conventional or expertise-based designs according to defined criteria to avoid biases from differential surgeon expertise. Mini-open or all-arthroscopic repair procedures will be performed according to a standardized protocol. Central Adjudication (of cases), Trial Oversight and Safety Committees will monitor trial conduct. We will use an analysis of covariance (ANCOVA), where the baseline WORC score is used as a covariate, to compare the quality of life (WORC score) at 2 years post-operatively. As a secondary analysis, we will conduct the same statistical test but will include age and tear size as covariates with the baseline score. Enrollment will require 2 years and follow-up an additional 2 years. The trial will commence when funding is in place.

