### Subjects

#### Inclusion/Exclusion criteria

We will recruit patients with small or medium-sized rotator cuff tears as determined by clinical examination and diagnostic imaging (MRI) prior to surgery. The full-thickness rotator cuff tears of supraspinatus and infraspinatus will be classified into 2 categories based on longest dimension: SMALL = 0–1 cm; MODERATE = 1–3 cm. Definitive measurement of tear size will be made in surgery and used as a covariate in analysis (JOINTS Canada measurement protocol will be used).

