#### Conventional RCT

Patients will arrive at their surgical consultation where the surgeon will assess patient eligibility during history and physical examination, taking into account diagnostic information provided from pre-consultation MRI. The surgeon will explain the clinical trial and that by agreeing to participate, the patient has a 50:50 chance of receiving either method (mini-open or all-arthroscopic) to repair the torn rotator cuff tendon. The research assistant will obtain informed consent and contact the central randomization computer to obtain patient identification number and treatment assignment.

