##### Control of biases through blinding

Surgeons cannot be blinded. However, the patient, the data collector, radiologist, and data analyst are blinded to group allocation for the duration of the study and data analysis. As the primary outcome is self-report, bias is minimized.

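### The primary ANCOVA is valid but forgoes a possible small precision gain from age and pre-operative tear size, and the adjusted model uses a tear size measured after randomisation

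*Protocol article*

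**What the plan says.** The Planned analyses section of the protocol article fixes the primary model: "In our primary analysis we will use an analysis of covariance (ANCOVA), where the baseline WORC score is used as a covariate". The abstract agrees, describing an ANCOVA "where the baseline WORC score is used as a covariate, to compare the quality of life (WORC score) at 2 years post-operatively". The next sentence of Planned analyses adds the supporting model: "As a secondary analysis, we will conduct the same statistical test but will include age and tear size as covariates with the baseline score".

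The Inclusion/Exclusion criteria section says which tear size is meant: "Definitive measurement of tear size will be made in surgery and used as a covariate in analysis".

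Allocation comes earlier than that. Under Conventional RCT, the surgeon assesses eligibility "taking into account diagnostic information provided from pre-consultation MRI". The research assistant then takes consent and makes contact to "contact the central randomization computer to obtain patient identification number and treatment assignment". The expertise-based design follows the same order. On masking, the blinding section states: "Surgeons cannot be blinded".

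The Sample size section uses the baseline-only ANCOVA, through a (1 − r²) term with r = 0.55.

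**The concern.** Prognostic covariates that are measured before randomisation and named in advance usually reduce residual variance. They also correct chance imbalance, and they do not inflate the type I error. The investigators thought age and tear size worth a second model but left them out of the test that decides the trial. Neither is a stratification factor (those are surgeon and compensation status), so the design does not restrict chance imbalance in them. The planned power is close to 80% at the analysed sample size, so inexpensive precision has some value.

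The second matter is timing. The tear size designated for adjustment is obtained during the assigned operation. If the two procedures expose or prepare the tear differently, or if knowledge of the arm affects the measurement, the covariate itself can differ by arm. Adjusting for it would then move the treatment estimate for reasons unrelated to prognosis. This affects the supporting model as planned. It would affect the primary result if the same variable were simply moved across.

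**Working it through.** **Inputs from the Sample size section:** SD σ = 450; r = 0.55; δ = 142.5 (taken as stated); "α = the probability of making a Type I error = 0.05", used two-sided with z = 1.96; power 0.80; 109 per group, 250 in total after 15% inflation.

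**Step 1. Reproduce the plan's figure.**
- Residual SD after baseline WORC: 450 × √(1 − 0.55²) = 375.8.
- N per group: 2 × (1.96 + 0.84)² × 450² × (1 − 0.55²) / 142.5² = 109.07, stated as 109.
- Total: 218 × 1.15 = 250.7, stated as 250.
- SE at 109 per group: 375.8 × √(2/109) = 50.9. Power: Φ(142.5/50.91 − 1.96) = 79.9%.

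The stated size therefore belongs to the baseline-only model and borrows nothing from age or tear size.

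**Step 2. Add two covariates.** Let p be the joint partial R² of age and tear size given baseline WORC. The documents give no value, so p is assumed over a range. The residual SD becomes 375.8 × √(1 − p).

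| p (assumed) | SE | Power at 109 per group | N per group for 80% power (exact z, rounded up) |
|---|---|---|---|
| 0 | 50.9 | 79.9% | 110 |
| 0.01 | 50.7 | 80.3% | 109 |
| 0.02 | 50.4 | 80.7% | 108 |
| 0.05 | 49.6 | 81.9% | 104 |
| 0.10 | 48.3 | 83.9% | 99 |

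**Step 3. Charge for the two degrees of freedom.** The table ignores this cost. Residual degrees of freedom fall from 218 − 3 = 215 to 218 − 5 = 213, which widens the SE by about √(215/213) = 1.0047. The gain and the cost cancel when (1 − p) × 215/213 = 1, so p = 2/215 = 0.009. With this factor applied, power is 79.6% at p = 0, 81.6% at p = 0.05 and 83.6% at p = 0.10.

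**Step 4. Illustrate the risk from the in-surgery tear size.** Suppose the recorded size differs between arms by m SD purely because of how it is measured, and its own partial R² is p. Adjusting for it shifts the treatment estimate by about 375.8 × √p × m. With m = 0.2 and p = 0.05 (both assumed): 375.8 × 0.2236 × 0.2 = 16.8 points, or 12% of δ. With m = 0.1 and p = 0.02 the shift is 5.3 points (4% of δ). With m = 0.3 and p = 0.10 it is 35.7 points (25% of δ).

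**Step 5. Check that a pre-randomisation value exists.** Eligibility rests on pre-operative MRI, which is in hand at the consultation. The Complications/Cuff integrity section also plans to compute change in tear size from the pre-operative state, so a pre-operative size has to be recorded.

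**The case against.** The strongest reply is that nothing here is wrong. The primary model is prespecified, is stated consistently in the abstract and in Planned analyses, and matches the sample-size formula. A simple primary model with a named adjusted model behind it is accepted practice. All of that stands. The hierarchy is also clear, so it would be unfair to call the two models competing results; the proposed change would report two models as well.

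A reader might infer that the plan gives away precision on its own chosen covariates at no saving. The documents do not support that. The tear-size covariate the plan chose is the in-surgery one, and leaving it out of the primary model protects that comparison. Nor is any loss of precision demonstrated, because no association of age or tear size with 2-year WORC is reported. There are reasons to expect a modest one. Eligibility confines tears to 3 cm or less, which narrows the range. The Secondary objectives section notes that self-report scores are poor indicators of imaging findings. The pre-operative scan is also an imperfect guide to what surgery finds.

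What survives is narrower. Age and a pre-operative tear size precede allocation and cost almost nothing to include, and the tear size now named for adjustment is measured at the wrong time.

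**Conclusion.** This is a small, optional improvement to the primary model, together with a clearer correction to the covariate in the adjusted model. The baseline-only ANCOVA is sound and could stand. Adding age and pre-operative tear size would bring about 0 to 4 power points (79.9% up to at most 83.9% at 109 per group) if their joint partial R² lies between 0.01 and 0.10. Below about 0.01 there is no gain. Those R² values are assumptions.

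The objection to the in-surgery tear size follows from the order of events in the document and does not depend on assumed R² values. Only the size of a possible shift does, and the documents do not show that any shift would occur.

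**What to change.** In Planned analyses, and correspondingly in the abstract:

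1. State the primary model as 2-year WORC on arm, baseline WORC, age and pre-operative imaging tear size.
2. Keep the ANCOVA on baseline WORC alone as the sensitivity analysis.
3. In Inclusion/Exclusion criteria, stop designating the in-surgery measurement as the analysis covariate. Use the pre-operative imaging value in every adjusted model and keep the surgical measurement for description.
4. Say in advance what is done for a patient without a usable pre-operative MRI size. The article provides ultrasound where MRI is contraindicated, so the covariate is better defined as an imaging size than as an MRI size.

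The sample size need not change, since it already holds without the extra covariates. The change is one of wording, using data already planned for collection. It costs about two degrees of freedom (SE wider by about 0.5% if the covariates explain nothing) and accepts a less definitive measure of the tear in exchange for one that allocation cannot influence. It should be made before outcome data are seen.
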